### Outcomes

#### Primary outcome

The primary outcome will be the total number of encounters with hospital, medical, and health services for LBP (composite measure) [30] over 12 months from baseline assessment. The number of encounters of using hospital, medical, and health services for LBP could be related to a new or ongoing episode of LBP. Data will be collected at baseline, 6- and 12-months from baseline assessment, as well as fortnightly during the 12-month follow-up period, via online (electronic) self-reported questionnaires specifically designed for this study (see Additional file 3, Additional file 4, Additional file 5). Data will also be collected via linkage to participants’ Medicare Benefits Schedule and Pharmaceutical Benefits Scheme data. Encounters with hospital, medical, and health services for LBP will be defined as: (1) a visit to any hospital service due to LBP (e.g., emergency department presentations, inpatient admissions/hospitalisations, outpatient services (e.g., outpatient physiotherapy, pain clinics), surgical procedures due to LBP); (2) a visit to a community-based medical or health practitioner due to LBP (e.g., general practitioner, specialist clinician, physiotherapist); (3) any diagnostic test for LBP (e.g., imaging); (4) a visit to any hospital, medical and health services to receive or fulfill a script for prescription medications, or a visit to any non-hospital Medicare services for LBP. Data on item 4 will be obtained through linkage to participants’ Medicare Benefits Schedule and Pharmaceutical Benefits Scheme data. Each encounter described above will be counted as an individual visit (e.g., a participant receiving 8 sessions of physiotherapy treatment will be considered as having 8 encounters). To account for data dependency, multiple encounters which occur within a 24-h period will be counted as one encounter.

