**ASSESSMENTS**:						
*Use of hospital, medical, and health services for LBP*		X		X	X	X
*Self-reported physical activity levels*		X			X	X
*Objective physical activity levels*		X			X	
*Physical Function*		X			X	X
*Pain intensity*		X		X	X	X
*Disability*		X			X	X
*Quality of life*		X			X	X
*Self-management behaviours*		X		X	X	X
*Medication use*		X		X	X	X
*Sleep quality*		X			X	X
*Attitudes regarding use of pain medications*		X			X	X
*Beliefs about back pain*		X			X	X

^a^ From baseline assessment (week 0)

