#### Inclusion criteria

Potential participants will need to meet all the following inclusion criteria:
i)18 years of age or older;ii)presentation of non-specific LBP of at least 12-week duration, with or without leg pain but without radicular (e.g., reflex changes, motor loss) symptoms. Non-specific LBP will be defined as LBP without diagnosis of a specific cause, and the absence of serious spinal pathology or indicators of potentially serious conditions using ‘red’ flags;iii)recently discharged (< 4 weeks post-treatment) from outpatient physiotherapy treatment from a participating hospital site. This includes discharge from one-to-one physiotherapy care directly into the community, or from supervised group exercise programs offered by the outpatient physiotherapy department;iv)have adequate hearing and eyesight to participate safely in physical activity;v)independent ambulatory status, with or without a gait aid.

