### Recruitment

#### Participant identification

Physiotherapists from the outpatient musculoskeletal physiotherapy departments of participating hospital sites will identify (all) patients who are within 1–2 weeks of their anticipated discharge from physiotherapy treatment for chronic LBP. The physiotherapist will introduce the study to all candidate patients. For patients indicating interest in participation, their contact details will be provided to the research team. The research team will phone the potential participant to provide them with further information about the study, including the study documents. Those who confirm their interest in the trial will be invited to take part in the consent procedures with a research team member, which will ideally occur within 1–2 weeks prior to discharge from treatment. De-identified demographic data (age, sex) and LBP pain scores at discharge from treatment (assessed with the NRS) will be collected from all candidate patients, irrespective of their interest or provision of consent. Data will be used to assess selection bias and target population reach.

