### Baseline assessment

Depending on participant preference, baseline assessment will occur face-to-face at the hospital site with a research assistant, or remotely. For participants completing baseline assessment remotely, a research team member will be available to provide support via phone call or video-conferencing software. Participants will be required to complete an online (electronic) baseline questionnaire to record demographic and anthropometric data (age, height, weight), and the study outcomes (see Additional file 3). In addition, participants will be given a tri-axial accelerometer (Axivity) to wear for 7 consecutive days on their right thigh. During the 7-day period, participants will be asked to document any physical activities or exercises completed in a paper-based logbook (see Additional file 7). After 7 days, participants will return the accelerometer and logbook to the research team via a pre-paid reply envelope. At baseline assessment, all participants will also receive a paper-based weekly diary (see Additional file 8) to document any adverse events which may occur during the intervention period (6 months) - see below. For participants who complete the baseline assessment at the hospitals, the online baseline questionnaire will be completed on-site and the research team member will directly attach the accelerometer onto the participant’s thigh. For participants who complete the baseline assessment remotely, they will receive a link to the online baseline questionnaire via SMS or email, and any relevant study documents and equipment will be posted to them. The participant will receive a detailed sheet with labelled images and instructions on how to self-attach the accelerometer device (see Additional file 7). As required, a research team member will be available to provide support for any baseline assessment procedures, via phone call or video-conferencing software.

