### Randomisation

After baseline assessment has been completed and the participant has been discharged from treatment, participants will be randomised with 1:1 allocation ratio to either the support system or usual care group. Treatment allocation will be performed using a computer-generated random allocation schedule operated by a remote unblinded researcher to ensure concealment. As participants will be randomised after discharge from treatment, with minimal potential for treatment contamination, randomisation will be at participant level. Randomisation will be by random permuted blocks of 4 and 6. Participants will be notified of their allocation via phone call from an unblinded research assistant. Select members of the research team will be unblinded to treatment allocation (i.e., main trial co-ordinator, the designated investigator managing referrals to the Get Healthy Service®, unblinded statistician monitoring trial safety, health coaches and agents from the Get Healthy Service®). Otherwise, all other research team members will remain blinded to treatment allocation. Participants will not be blinded to group allocation.

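### The 12-month primary count starts at baseline, before randomisation, so encounters the support system cannot affect enter the endpoint and dilute the rate ratio; the order of baseline and discharge is also left unclear

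*Protocol article*

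**What the plan says.** **Start of the count.** The Primary outcome section counts "the total number of encounters with hospital, medical, and health services for LBP (composite measure) [30] over 12 months from baseline assessment". The Statistical analysis section uses the same 12 months from baseline, the footnote to Table 1 dates all follow-up from baseline (week 0), and Follow-up data collection times the 6- and 12-month questionnaires from baseline.

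**Randomisation.** The Randomisation section states: "After baseline assessment has been completed and the participant has been discharged from treatment, participants will be randomised with 1:1 allocation ratio". Baseline therefore always comes first, and discharge is listed as a separate condition.

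**Order of baseline and discharge.** Four places bear on this:
- Participant identification, on consent: "which will ideally occur within 1–2 weeks prior to discharge from treatment".
- Consent and screening goes from consent to formal screening and then invites eligible participants to baseline. It does not say to wait for discharge.
- Inclusion criterion iii requires the participant to be "recently discharged (< 4 weeks post-treatment) from outpatient physiotherapy treatment".
- Table 1 puts consent and screening at weeks -4 to -1, and baseline and allocation both at week 0.

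**What counts.** Outpatient physiotherapy is a listed encounter type, each session counts separately (unless within 24 hours of another encounter), and ongoing episodes are included. No exclusion is given for the index course or for encounters before randomisation.

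**Length of baseline.** The Baseline assessment section includes a week of accelerometer wear: "After 7 days, participants will return the accelerometer and logbook to the research team". Consent and screening adds that some participants need medical clearance before randomisation.

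**The concern.** A randomised comparison of encounter rates should count events that allocation could have influenced. Here the window opens earlier. Any LBP encounter between baseline and randomisation is scored as an outcome although the support system has not yet been offered. An offset for follow-up time does not help, because the early encounters stay in the count.

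The stated aim is use of services after discharge. If baseline takes place while the physiotherapy course is still running, its last sessions would count as outcome events, although they belong to the treatment the participant is being discharged from.

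At stake are the size of the estimated effect and some power. The window also holds slightly less than 12 months after randomisation.

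**Working it through.** **1. The plan's own figure.** The Sample size calculation gives 374 participants (187 per group) for 90% power at the 5% level, IRR 0.70, base rate 0.2, R² 0.09 and 10% loss. A two-sided Poisson-regression formula with a 50:50 predictor is

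N = (1.960·√4 + 1.282·√(2 + 2/0.70))² / (0.2 · t · (ln 0.70)²) / (1 − 0.09) / (1 − 0.10).

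It gives 2183 for exposure t = 1 and 84 for t = 26 fortnights; only an unstated t of about 6 comes near (364). The article gives neither mean exposure nor dispersion, so 374 cannot be rebuilt from the text. The assumptions below replace the missing inputs, and the direction of the bias does not depend on them.

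**2. Direction.** Let m be the usual-care mean after randomisation, 0.70m the intervention mean, and c > 0 the mean number of encounters before randomisation, equal in both arms. The observed ratio is (0.70m + c)/(m + c), which exceeds 0.70 for any c > 0. With no true effect it is (m + c)/(m + c) = 1, so no false benefit arises.

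**3. Time gap only (baseline after discharge).** With a gap of g weeks and the same background rate before and after randomisation, the rate cancels: IRR = (0.70·(52 − g) + g)/52.
- g = 1: 36.7/52 = 0.706
- g = 2: 37.0/52 = 0.712
- g = 4: 37.6/52 = 0.723

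**4. Remaining index sessions (baseline before discharge).** Assume 5.2 encounters per person-year in usual care. This reads the base rate of 0.2 as per person per fortnight: 0.2 × 26 = 5.2, and 0.70 × 5.2 = 3.64. Then IRR = (3.64 + c)/(5.2 + c), with c averaged over all participants.

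Power uses 187 × 0.9 = 168.3 per arm and the effective size 168.3 × 0.91 = 153.2. The dispersion k is chosen so that the undiluted design has 90% power. That requires 1/5.2 + 1/3.64 + 2k = 153.2 × (ln 0.70)²/(1.960 + 1.282)² = 1.854, hence k = 0.694. Power = Φ(|ln IRR|/SE − 1.960), where SE² = (V₀/μ₀² + V₁/μ₁²)/153.2 and μ₀, μ₁ are the diluted means. In the independent-noise case, V = 5.2 + 0.694·5.2² + c in usual care, and likewise with 3.64 in the intervention arm. In the shared-dispersion case, V = μ + 0.694·μ².

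| c (assumed) | IRR | Power, independent Poisson noise | Power, shared dispersion |
|---|---|---|---|
| 0 | 0.700 | 90% | 90% |
| 0.5 | 4.14/5.70 = 0.726 | 89% | 84% |
| 1 | 4.64/6.20 = 0.748 | 88% | 77% |
| 2 | 5.64/7.20 = 0.783 | 87% | 64% |
| 3 | 6.64/8.20 = 0.810 | 85% | 53% |

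For the gaps in step 3, at 5.2 per year, power is 89 to 90% with independent noise and 84 to 89% with shared dispersion.

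**5. Sensitivity to the annual rate.** At an assumed 2 encounters per year, c = 1 gives 2.4/3 = 0.80 and c = 2 gives 3.4/4 = 0.85. A lower true rate makes the same number of early sessions weigh more.

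**6. How far before discharge baseline could fall.** Take consent 1 to 2 weeks before discharge, and baseline 1 to 4 weeks after consent (Table 1). Baseline then lies between −2 + 1 = 1 week before and −1 + 4 = 3 weeks after discharge. On this reading only some participants could have index sessions left, and for about a week at most.

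**The case against.** Criterion iii, read literally, requires prior discharge, and only participants found eligible are invited to baseline. If that rule governs, no index session can follow baseline, and only the small shift in step 3 remains. Table 1 puts baseline and allocation in the same week, and the article does not say that the accelerometer week must end before randomisation, so the gap may be short. Consent before discharge is described as ideal, not as a rule. The annual rate, the dispersion and the session numbers are all assumptions.

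Much of this stands. It makes the index-session part conditional and supports an average c at the low end of the table. It does not remove the point. Discharge appears in the Randomisation section as a condition separate from baseline, and that condition would be redundant if baseline always followed discharge. The consent flow permits the earlier order, and no counting rule excludes encounters before randomisation under either order.

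A reader might infer more: that leftover sessions certainly enter the endpoint for every participant, that power falls to about 53 to 77%, or that the trial's inference is invalid. The documents do not support this. Criterion iii contradicts the first. The low power figures need a few scheduled sessions to carry the same overdispersion as a year of care-seeking, and 1 to 3 of them for everyone. The bias is towards no effect, so a positive result would not be undermined.

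**Conclusion.** The point holds in a limited form. It is certain from the text that the primary count opens before randomisation, that nothing excludes the encounters in between, and that any such encounters dilute a true effect. Whether index physiotherapy is also counted depends on sections that contradict each other.

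The size cannot be determined from the documents. With baseline always after discharge it is slight: 0.70 becomes about 0.706 to 0.723 for an assumed gap of 1 to 4 weeks. With remaining index sessions it can be material: about 0.73 to 0.81 for an assumed average of 0.5 to 3 sessions per person at an assumed 5.2 encounters per year. Power then falls by about 1 to 5 points if the added counts are independent noise, and by more only if they share the overdispersion. The plan should be corrected, because the change is nearly free and concerns the primary endpoint, but this is not a fatal flaw.

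**What to change.** - Define time zero as the date of randomisation, after discharge, for the primary count, the follow-up-time offset and the cost window.
- Count only encounters dated after randomisation, up to 12 months. The existing rule that merges encounters within 24 hours already presupposes that timing is known.
- Treat encounters between baseline and randomisation as baseline data.
- Trigger the fortnightly, 6-month and 12-month questionnaires from the same date. This also brings the 6-month assessment closer to the end of the 6-month coaching period, which can only start after randomisation and referral.
- Reconcile Table 1, inclusion criterion iii, Participant identification, Consent and screening, and Randomisation on whether baseline may precede discharge. Either order can work once the count starts at randomisation, but the sections must agree.

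**Cost.** Wording in the protocol and analysis plan and a changed trigger date in the questionnaire system, with no extra participants or visits. Baseline measures will lie slightly further from the follow-up assessments. The change is best made before the recruitment start of July 2021 given under Trial status.

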### Sample size calculation

The sample size is that required to detect a clinically meaningful between-group difference in the primary outcome, i.e., the total number of encounters with hospital, medical, and health services for LBP [44]. A total of 374 participants (*n* = 187 per group) will be recruited. The study will have 90% power to detect as significant, at the 5% level, a 30% difference in the rate of using hospital, medical, and health services for LBP between groups (i.e., an Incidence Rate Ratio of 0.70 using negative binomial regression analysis) over the 12-month study period. The 30% difference in the rate of using hospital, medical, and health services for LBP is based on our research of patients’ perceptions of a clinical worthwhile effect of interventions for LBP [45]. Estimates were based on a base rate exposure (β0) of 0.2 [total of 2 care-seeking events in the usual care group per fortnight (data from pilot)], assuming a correlation of 0.3 (R^2^ = 0.09) between covariates and predictor (treatment), using negative binomial regression model (G*Power® software) [46]. Estimates allow for a loss to follow-up of 10%.

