### Statistical analysis

The total number of encounters with hospital, medical, and health services for LBP per person, over 12 months from baseline assessment, will be analysed using negative binomial regression to estimate the between-group difference in the rate of using hospital, medical, and health services for LBP at 12-month follow-up. Negative binomial regression takes into account individual follow-up time, frequency of using hospital, medical, and health services for LBP, non-normal distribution over time, and non-independence of repeated measures [44]. The effect of baseline pain and disability levels, number of previous treatments, symptom length, co-morbidities, and age will be accounted for in the model. The effect of group allocation on continuous outcomes (e.g., physical function, physical activity) will be assessed using linear regression models. All analyses will be performed by intention to treat.

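### The 24-hour merge and the negative binomial model are each credited with handling dependency, but neither protects the primary p-value and interval if the count shape is wrong, and no robust variance is stated

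*Protocol article*

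**What the plan says.** Under Primary outcome, the protocol article defines one composite total per participant over 12 months. It covers hospital visits, community practitioner visits, diagnostic tests and prescription-related visits. Each visit counts: "a participant receiving 8 sessions of physiotherapy treatment will be considered as having 8 encounters". The next sentence is "To account for data dependency, multiple encounters which occur within a 24-h period will be counted as one encounter".

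Under Statistical analysis, this total "will be analysed using negative binomial regression to estimate the between-group difference in the rate of using hospital, medical, and health services", with adjustment for several baseline covariates. The same section lists what the model is said to take into account. The list includes follow-up time, frequency of use, "non-normal distribution over time, and non-independence of repeated measures".

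The Randomisation section says "randomisation will be at participant level". The Sample size calculation gives 187 per group, with 10% loss allowed. The article does not say how the standard error of the rate ratio will be estimated.

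**The concern.** Both statements tell the reader that dependency has been dealt with. The merge removes only encounters within the same 24 hours. One decision to start physiotherapy can still add 8 events on 8 days, and a general practitioner visit, imaging or a script on other days adds more. The yearly total may therefore mix people with few or no visits and people with batches of visits.

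The negative binomial model does allow for overdispersion, but of one particular form: person-level rates that vary as a gamma distribution. Its model-based standard error is right only if that form holds. What is at stake is the p-value and confidence interval of the single primary test. They could be too wide, losing power, or too narrow, giving false positives. The rate ratio itself is not in doubt: with two arms, equal follow-up and no covariates, the fitted ratio is simply the ratio of the arm means.

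**Working it through.** **Inputs from the article.** 187 per group less 10% gives 187 × 0.9 ≈ 168 analysed per arm. The target rate ratio is 0.70, the level 5% (taken as two-sided) and the power 90%. The base rate of 0.2 is read as per person per fortnight, so 0.2 × 26 = 5.2 encounters per year. That reading is an assumption.

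**The plan's own figure.** With μ₀ = 5.2, μ₁ = 0.7 × 5.2 = 3.64 and dispersion k, the evaluable total is

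N = 2(1.96 + 1.2816)² × [(1/μ₀ + k) + (1/μ₁ + k)] / (ln 0.7)² / (1 − 0.09) = 181.5 × (0.467 + 2k).

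With k = 0 this is 85. The planned 374 × 0.9 ≈ 337 needs k ≈ 0.69. The article states no dispersion and no mean exposure, so 374 cannot be reproduced. That does not show it to be wrong and is not part of this point. The value k = 0.69 only sets the reference scenario below.

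**Mechanism.** For two arms of size n under no effect:

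- model-based variance of the log rate ratio: 2(1/μ + k_ML)/n
- actual sampling variance: 2(1/μ + k*)/n, with k* = (Var(Y) − μ)/μ²

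The two agree when the maximum-likelihood k_ML equals k*, which is assured only if the counts are negative binomial. The approximate type I error is 2[1 − Φ(1.96r)], where r is the ratio of the two standard errors. Three assumed shapes:

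- *Only 8-session courses* (number of courses negative binomial, mean 0.5, dispersion 1): μ = 3.99, k_ML = 7.65, k* = 2.76. r = √[(0.25 + 7.65)/(0.25 + 2.76)] = 1.62, type I error about 0.0015 (simulated 0.001).
- *Care episodes, 40% of them 8-session courses and the rest single visits:* μ = 5.70, k_ML = 3.05, k* = 2.03. r = √[(0.175 + 3.05)/(0.175 + 2.03)] = 1.21, about 0.018 (simulated 0.017).
- *Poisson background of 2, plus 5% of people with 30–60 further visits:* μ = 4.24, k_ML = 1.48, k* = 5.44. r = √[(0.236 + 1.48)/(0.236 + 5.44)] = 0.55, about 0.28 (simulated 0.289).

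The error can therefore go in either direction.

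**Simulation at a usual-care mean of about 5.2.** 4,000 trials per scenario, 168 per arm, negative binomial maximum likelihood, with model-based and sandwich standard errors taken from the same fit. The Monte Carlo standard error at 0.05 is √(0.05 × 0.95/4000) ≈ 0.0034.

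| Assumed count shape | Type I error, model-based | Type I error, sandwich | Power at 0.70, model-based | Power at 0.70, sandwich |
|---|---|---|---|---|
| Negative binomial, k = 0.69 | 0.059 | 0.059 | 0.929 | 0.929 |
| Single visits, 21% also have one 8-session course | 0.029 | 0.046 | 0.827 | 0.875 |
| Episodes, 32% of them 8-session courses | 0.023 | 0.049 | 0.427 | 0.537 |
| 8-session courses only | 0.003 | 0.057 | 0.126 | 0.499 |
| Low background, 10% with 8–36 further visits | 0.162 | 0.057 | 0.778 | 0.562 |
| Low background, 6% with 24–50 further visits | 0.223 | 0.058 | 0.722 | 0.411 |

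Over these scenarios, at rate ratios of 1 and 0.70, coverage of the 95% interval was 0.739 to 0.998 model-based and 0.937 to 0.954 with the sandwich. Two further mixtures of visits and courses, at other means, gave model-based type I errors of 0.038 and 0.040. A separate simulation with 8% heavy users gave 0.12. Over all the 4,000-trial scenarios, including those at other means, the sandwich stayed within 0.046 to 0.066.

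In the last two rows the model-based power is higher only because its intervals are too short. The sandwich corrects the error rate; it does not restore 90% power.

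**The case against.** **The estimator is not stated.** A reader might infer that the primary test is planned on the model's own variance and is therefore invalid. The article does not say so. It names the regression model only, a robust variance is compatible with that wording, and such detail is commonly left to the SAP, which is not shown. This objection stands, and it makes the point conditional.

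**The merge is not the only answer offered.** The Statistical analysis section also relies on the model. With individual randomisation and one total per person, sessions of a course are not correlated observations in the analysis. They add up to one count, and their clustering appears as overdispersion, which the model is built to accommodate. That is right as far as it goes. What remains is that the accommodation holds for one shape, and the article claims it without that limit.

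**Counting every session is legitimate.** A reader might infer that the outcome ought to count episodes instead. The documents do not support that: total encounters is an explicit choice for a utilisation outcome, and nothing here depends on changing it.

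**The sizes rest on assumed distributions.** This also stands. The article gives no count distribution. Its 21% re-presentation figure covers hospital services in one district, whereas the outcome also counts community care. The plausible mixtures of visits and courses made the test only mildly conservative; large inflation needed a heavy tail. The simulations omit covariates and unequal follow-up, and the planned covariates may explain part of the heavy use.

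**Conclusion.** The concern holds in a limited form. The article claims more for the 24-hour merge and for the negative binomial model than either delivers, and it states no robust variance. If the model-based standard error is used, the validity of the primary p-value and interval depends on a distributional shape that the session-by-session counting rule makes doubtful.

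Under the assumed shapes, type I error at a nominal 5% runs from well below 1% (courses only), through 2% to 3% (mixed visits and courses), to 12% or more (a few very frequent users). The sandwich variance gives about 5% to 6%. If the counts are truly negative binomial, the two variances behave alike. These figures assume 168 per arm, a mean near 5.2 per year in the main comparison, equal follow-up and no covariates. Since the true distribution is unknown, neither the size nor the direction of any error in this trial can be stated.

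**What to change.** Keep the encounter count and the negative binomial rate ratio. Prespecify that the primary confidence interval and p-value use a robust (sandwich) variance, or confirm this if the SAP already says so.

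Narrow the two claims. Under Primary outcome, describe the 24-hour rule as removing same-day duplicates. Under Statistical analysis, say that the model allows for overdispersion of the per-person total, without claiming that it deals with non-independence in general.

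The cost is a sentence in the analysis plan and two wording changes. No new data are needed and the rate ratio does not change. In the truly negative binomial scenario, type I error (0.059) and power (0.929) were the same with either variance.
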